**Hypothesis:**

Remote IPC reduces post-CPB release of markers of cellular injury and permits recovery of cardiac pump function with less complication including inotrope requirement in patients undergoing congenital heart surgery.

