**Aim:**

To assess the impact of remote IPC on lactate release, inotrope requirement, and standard clinical cardiopulmonary assessments in response to heart surgery with CPB support.

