**Secondary outcome measures:**

Alveolar-arterial (A-a) oxygen gradient and lung compliance will be obtained as a part of routine clinical assessment. Measures of lung function oxygenation index and alveolar-arterial oxygen gradient at 3, 6, 12, 24 hours post-op. Measurements including mean systemic arterial, and right atrial pressures are made at 3, 6, 12, and 24 hours after aortic cross clamp release. The doses of inotropic, chronotropic, and afterload reducing agents at the time of the cardiac output measurements are recorded. For between-group comparisons, a total inotrope dose score is calculated by adding the doses of dopamine and dobutamine in micrograms per kilogram per minute and assigning an arbitrary equivalent value of 10µg•kg-1•min-1 inotrope for each 0.1µg•kg-1•min-1 epinephrine. Daily post-operative measurements of arterial blood gases, serum glucose, calcium, electrolytes, hematologic parameters, arterial lactate, blood urea nitrogen, and creatinine, the total volume and type of fluid intake, urine output, and chest tube drainage, the total hours of mechanical ventilation and the days in the CICU and the hospital are recorded.

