# SUBJECT ENROLLMENT AND RANDOMISATION

- 1. **Recruitment**

Patients will be recruited by either the surgeon ([name]) or cardiologist ([name]) at the preadmission clinic or on the ward prior to surgery. The clinician ([name]/[name]) will explain to the patient’s parents/guardians, the research project, their child’s role, and outcomes and will obtain signed consent if granted.

- 1. **Eligibility Criteria**
     1. **Inclusion Criteria**

Patients with tetralogy of Fallot aged one month and older (to 18 years) having surgery for the first time.

- - 1. **Exclusion Criteria**

Patients with chromosomal defects, associated congenital lung malformations and haematological disorders will be excluded.

- 1. **Randomisation Procedures**

Random allocation is made in blocks in order to keep the sizes of the 2 treatment groups similar. In order to avoid predictability, the block size that is randomly selected is 2, 4 or 5, as the sample size must be divisible by the block size. Due to the expected relative uniformity of condition in the patient group and the small number of subjects the design will not be stratified. The randomisation will be performed in secret by a member from Heart Research (not involved in working for the trial) using SPSS statistical software generated randomisation and will place each designation sequentially in numbered envelopes 1 to 40, for patient 1 to 40 and the envelopes will be signed and sealed. The implementer of the RIPC or Sham co ntrol treatment protocols will open one envelope in numerical order immediately prior to placement of the blood pressure cuff and they will apply the RIPC treatment or sham control protocol accordingly.

- 1. **Blinding Arrangements**

[name] will not be blinded as she will be applying the RIPC treatment. She will also be involved in randomisation, sample collection, data collection, data entry and laboratory analysis. Surgeons, perfusionists, anaesthetists will be blinded. Samples will be de-identified and therefore, research laboratory staff will be blinded to the patient’s identity. The blood pressure cuff will be positioned on the thigh for both sham control and RIPC groups, however if other theatre staff witness whether the RIPC treatment protocol is invoked they will not be blinded. As these theatre staff are strictly performing standard clinical tasks and procedures and are not involved in the trial and analysis *per se*, this should not impact the blinding.

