# STATISTICAL METHODS

**10.1 Sample Size Estimation**

Sample size is based primarily on the successful study of RIPC in children (see ref 17) where n=approximately 20 per treatment group. This prior study was amply powered to detect differences in clinical and molecular measures. Notably, post-operative inotrope usage was greatly diminished by RIPC. Based on these inotrope usage results, a power of 0.8, alpha=0.05 and sigma of 3.9 indicates that a sample size of n=20 was required. Injury was deemed to be diminished by RIPC on the basis of reduced troponin I release, thus for a power of 0.8, alpha of 0.05 and a sigma of 3 the sample size required is calculated as n=16. Based on our laboratory’s ability to detect a 20% difference in mitochondrial oxygen consumption in human tissue preparations at least 10 subjects are required to detect this difference (power=0.8, sigma=14.5, alpha=0.05, 2 groups. Similarly, the detection of changes in many mitochondrial proteins measured by proteomic assays, are also quite sensitive ranging between 10-20%. Thus a sample size of n=20 per group will yield ample statistical power.

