**10.3 Statistical Analysis Plan**

Lab Assay analyses will be performed on coded samples by Drs [name] and [name] and the values then made available for statistical testing when all tests are complete. Statistical analyses will be performed by Drs [name], [name] & [name]. An independent professional statistician experienced in trials will be employed to check and verify the analyses prior to and after breaking the blinding. In addition to two-way ANOVA or unpaired t test, statistical analysis will employ stepwise multivariate regression and analysis of covariance tests in order to determine potential influence of age, gender, bypass time, drugs, body weight and other morphometric and clinical factors.

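### The covariate list in section 10.3 admits drugs and bypass time, which arise after allocation; adjusting for inotropes, an outcome of RIPC, can distort the adjusted estimate of its effect

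*Protocol*

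**What the plan says.** Protocol section 10.3 names two layers of analysis. The first is unadjusted: "In addition to two-way ANOVA or unpaired t test". The second is "stepwise multivariate regression and analysis of covariance tests in order to determine potential influence of age, gender, bypass time, drugs, body weight", and the list then continues with unnamed morphometric and clinical factors. The candidates are not limited to values known before allocation. The section does not say which layer decides if the two disagree.

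The timing is set elsewhere. Under Randomisation Procedures (6.3), the person applying the cuff "will open one envelope in numerical order immediately prior to placement of the blood pressure cuff". Section 5.1.2 places the cuff cycles straight after induction of anaesthesia. Bypass, and any drug given during or after surgery, come later.

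Inotropes appear in the protocol as an effect of treatment:
- Secondary hypothesis (3.2): RIPC "permits recovery of cardiac pump function with less complication including inotrope requirement".
- Secondary aim (3.2): "To assess the impact of remote IPC on lactate release, inotrope requirement".
- Secondary outcome measures (4.4): "The doses of inotropic, chronotropic, and afterload reducing agents at the time of the cardiac output measurements are recorded". An inotrope score is then built for comparison between groups.
- Sample size (10.1): in the earlier paediatric trial "post-operative inotrope usage was greatly diminished by RIPC", and n=20 is derived from that result.

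**The concern.** A covariate measured before allocation can sharpen a randomised comparison without biasing it. A covariate that treatment changes cannot be used in the same way. Conditioning on it takes out whatever part of the effect runs through it. If the covariate and the outcome share an unmeasured cause, such as how sick the child is after surgery, conditioning can also produce a difference between arms where treatment has none.

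Section 10.3 lists drugs without defining them. The drugs that the protocol says it records are inotropic, chronotropic and afterload-reducing agents, so the natural reading includes the variable that the protocol expects RIPC to reduce. At stake is the meaning of the adjusted RIPC estimate for the post-bypass blood measures and the clinical outcomes.

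**Working it through.** **1. The protocol's own figures.** Section 10.1 gives one complete calculation: a 20% difference, SD 14.5, power 0.8, alpha 0.05. Taking both on the same percentage scale, two-sided, the t-based answer is 9.3, rounded up to 10 per group. This agrees with the stated 10. The inotrope figure (SD 3.9, n=20) comes without a difference and can only be inverted. With 20 per arm, 80% power and two-sided 5%, the detectable difference is 0.909 SD, or 0.909 × 3.9 = 3.55 units. I use 0.91 SD as an assumed shift in inotrope dose. No stated figure is in dispute.

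**2. What adjustment does.** With dose as a covariate, on average:

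adjusted estimate = total effect − (within-arm slope of outcome on dose) × (shift in dose between arms)

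If the shift is zero, the adjusted and unadjusted estimates agree. If it is not, they differ by slope × shift.

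**3. Case A: part of the effect runs through dose.** Assume a shift of 0.91 SD, a direct effect of 0.5 SD, within-arm SD 1 and slope b. The documents give neither the direct effect nor b, so b is varied.

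- Total effect = 0.5 + b × 0.91, with standard error √(2/20) = 0.316.
- Adjusted effect = 0.5 + b × 0.91 − b × 0.91 = 0.5, with standard error about √[(1 − b²)(2/20 + 0.91²/38)].

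| b | Total effect | Adjusted SE | Power, unadjusted | Power, adjusted |
|---|---|---|---|---|
| 0.3 | 0.77 | 0.333 | 66% | 31% |
| 0.5 | 0.96 | 0.302 | 84% | 36% |
| 0.7 | 1.14 | 0.249 | 94% | 50% |

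Simulation of 3,000 trials per setting gave total effects of 0.78, 0.96 and 1.14, adjusted effects of 0.51, 0.50 and 0.50, and the same powers.

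**4. Case B: dose and outcome share a cause.** Assume a shift of 0.9 SD and within-arm correlation ρ; 4,000 simulated trials per setting.

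| ρ | True effect 0.90: adjusted estimate | Power after adjustment (unadjusted about 79%) | True effect 0: size of adjusted estimate | False positives at nominal 5% |
|---|---|---|---|---|
| 0.3 | 0.90 − 0.27 = 0.63 | 45% | 0.26 | 12% |
| 0.5 | 0.90 − 0.45 = 0.45 | 30% | 0.45 | 30% |
| 0.7 | 0.90 − 0.63 = 0.27 | 18% | 0.63 | 68% |

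The spurious effect takes the sign opposite to ρ × shift. With a true effect of 0.90 and no shift in the covariate, the adjusted estimate stayed at 0.89 to 0.91.

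**5. Stepwise selection alone.** With no treatment effect, arm kept in the model, entry at 0.05 and removal at 0.10, the type I error was 6.4%, 5.9% and 8.0% for 6, 10 and 15 candidates (3,000 runs, Monte Carlo margin about ±0.8 to 1.0 points). If arm were itself open to selection, which section 10.3 neither states nor rules out, it was left out in 47%, 69% and 82% of the trials with true effect 0.90 in step 4. The rate was about 20% when the covariate was unrelated to both arm and outcome.

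**6. Which outcomes are exposed.** Blood is drawn at baseline, at the end of bypass, and 6, 12 and 24 hours later (5.1.5). The post-bypass samples and the clinical outcomes can be affected. Myocardium is resected after cardioplegia (5.1.4), before any postoperative inotrope, so this path is closed for the myocardial assays. The baseline sample also precedes those drugs.

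**The case against.** The strongest reply is that the regression is additional. The t test or ANOVA stays, it respects the randomisation, and nothing above alters it. The stated purpose of the adjusted models is to look at the influence of other factors, which reads as exploratory. All of this stands. A reader might infer from step 3 that the trial itself drops from 84% to 36% power. It does not: that contrast is between the retained test and an added model.

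A reader might also infer that adjusting for bypass time breaks the randomised comparison. Bypass time does follow allocation, but no section says RIPC changes it. Surgeons, perfusionists and anaesthetists are to be blinded (6.4) and bypass follows usual practice (5.1.3). Without a shift, step 2 gives no bias of this kind.

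Drugs is undefined and could include preoperative medication. Reading it as inotropes is an inference from section 4.4, though a reasonable one.

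Two further strong readings are unsupported. One is that stepwise selection may discard the single strong prognostic factor, age. Eligibility is wide ("Patients with tetralogy of Fallot aged one month and older (to 18 years) having surgery for the first time"), but the protocol does not rank prognostic factors, expects a fairly uniform group and lists age first. The other is that the investigators are free to report the more favourable model. An independent statistician is to verify the analyses before and after unblinding (10.3), and the blind is to be broken only once the final analyses are complete (6.5). These safeguards are imperfect, since one unblinded team member also handles data entry and laboratory analysis, but they limit choosing a model by its result.

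A closed covariate list and the choice of decisive model may properly sit in a statistical analysis plan. Their absence here is not the point. The point is that the protocol names, as candidates, a category that includes one of its own outcomes.

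**Conclusion.** The concern holds for drugs, and for post-bypass blood measures and clinical outcomes. As written, section 10.3 allows the RIPC effect to be adjusted for inotrope use, which the protocol expects RIPC to reduce. The result can be too small or spurious. The sizes are illustrations: they rest on an assumed dose shift of about 0.9 SD, an assumed direct or total effect, and an assumed slope or correlation of 0.3 to 0.7, none of which the documents give. Within that range the adjusted estimate loses between about a third and 70% of the total effect (0.77 to 0.50 at the least in case A, 0.90 to 0.27 at the most in case B).

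The concern is weaker for bypass time, does not reach the myocardial assays through postoperative inotropes, and leaves the unadjusted test intact. Stepwise selection adds only slight type I inflation, and would be a minor matter alone.

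**What to change.** Reword the last sentence of section 10.3 to this effect:

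- The treatment effect is estimated with arm always in the model and a short list of baseline covariates fixed in advance: the outcome's baseline value where one exists, and age or weight.
- Stepwise selection is not used for the treatment comparison.
- Bypass time and drugs given during or after surgery are reported by arm, or examined in a separate analysis labelled exploratory. They are not covariates in the treatment comparison.

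This changes analysis wording only; no procedure, sample or data item is affected. The cost is that associations with bypass time and drugs become exploratory only.

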**10.4 Interim Analyses**

Due to the brief study period and small number of subjects, an interim analysis is not scheduled.

# DATA MANAGEMENT

**11.1 Data Collection**

Clinical data will be collected by [name], Laboratory data will be collected by Drs [name] and [name] and [name].

**11.2 Data Storage**

Data will be stored coded on the secured laboratory computers in Heart Research and Haematology Research of MCRI.

- 1. **Study Record Retention**

Records will be maintained until the youngest participant is 25 years old.

# ADMINISTRATIVE ASPECTS

- 1. **Confidentiality**

Confidentiality is maintained per standard clinical and scientific practice at RCH/MCRI.

Samples and results are coded and stored separately to patient identifying details in a secured laboratory and office of Heamatology research, and Heart Research, Dept of Cardiology. No patient will be identified in any scientific publication or general lay report. Only patient group findings will be reported.

- 1. **Participant Reimbursement**

Not applicable.

- 1. **Financial Disclosure and Conflicts of Interest**

No financial disclosures or conflicts of interest to report.

# USE OF DATA AND PUBLICATIONS POLICY

Following conclusion of the study a lay report of the findings will be made available to all participant families, and the scientific results will be published in an international medical journal.

# TRIAL REGISTRATION

Registration of this study with the Australian Clinical Trials Registry will be completed upon Human Research Ethics Committee approval of the trial and prior to the commencement of recruitment.

**16. APPENDIX**

# SINGLE SERIOUS Adverse Event (SAE) REPORT FORM

- **All** Internal* SAEs (occurring to RCH participants) **must be reported to the RCH HREC within 24-72 hours of occurrence and must be accompanied by a detailed report of the event.**
- External SAEs (occurring to participants from other sites) **must be reported in a prompt manner if the information impacts the continued ethical acceptability of the trial or requires documentation to be updated (i.e. protocol or PIS).**

***An Internal SAE is one occurring in a participant that RCH researchers are responsible for, this is independent of where the event occurs.**

***Please complete this form electronically and then print.***

***Please submit 1 original & 2 copies of this form along with all supporting documentation.***

| **HREC# :** |
| --- |

| **Study Title** (inc protocol #) **:** |
| --- |

| **Date that SAE occurred :**  **Date Investigator became aware of SAE :** |
| --- |

| **Participant ID :** |
| --- |

| **Internal or External (see above definition):** |
| --- |

| **Event details (synopsis):** |
| --- |

| **Event management (synopsis):** |
| --- |

| **Event outcome (synopsis):** |
| --- |

**Investigator’s opinion of the Serious Adverse Event:**

Expected  Unexpected

**Investigator’s opinion of the Serious Adverse Event relationship to the study drug:**

**Unrelated**  **Possibly related**  **Probably Related**  **Definitely Related**

| **Other (provide details) :** |
| --- |

Does the protocol require amending as a result of this SAE? **Y**  **N**

### If Yes, please submit a modification request with the amended protocol.

Do the information/consent forms require amending as a result of this SAE? **Y**  **N**

